#### 2.a.3. *Safety, tolerability and dosing*

The proposed study is grounded in the use of established clinical and experimental methods. In all previous studies of mifepristone in neuropsychiatric disorders, a pulse dose strategy has been employed with administration of mifepristone for 4-8 days. The majority of these studies used a dose of 600 mg/day (Belanoff et al., 2001; Belanoff et al., 2002; Young et al., 2004; Simpson et al., 2005; Gallagher et al., 2005; Flores et al., 2006; DeBattista et al., 2006; Blasey et al., 2009); 1200 mg/day has been studied in psychotic depression (Belanoff et al., 2002) and is being used in current studies of mifepristone in psychotic depression. In a recent Phase III trial of 600 mg/day of mifepristone in psychotic depression, a dose-response relationship between plasma concentration of mifepristone and treatment response was found. Only about one-third of the participants achieved what was previously determined to be the optimal blood level of mifepristone in depression. If a similar dose-response relationship exists in PTSD, some participants would need a higher dose of mifepristone to achieve clinical response; yet, in our pilot data there is preliminary evidence of a treatment effect at 600 mg/day. Accordingly, we will examine the effects of 600 mg/day of mifepristone and post-treatment mifepristone levels on clinical response. According to [name], rash is estimated to occur in 1% of persons treated with 300 mg/day of mifepristone, 3.3% of persons treated at 600 mg/day, and 5.5% of persons treated with 1200 mg/day (Corcept Therapeutics).

With respect to HPA axis activity, based on the results of the ACTH and CRF stimulation tests, pituitary and adrenal reserves are maintained during mifepristone treatment (Bertagna et al., 1994). Chronic treatment with mifepristone does not appear to be associated with the development of iatrogenic adrenal or pituitary insufficiency. Based on published reports and personal communication with [name] of Corcept Therapeutics, adrenal insufficiency has never been observed with one week of mifepristone treatment in depressed patients. (See also the section on monitoring adverse events, 4.i., for details on safety monitoring.) Nonetheless, since mifepristone is contraindicated in adrenal insufficiency, for safety reasons participants with a known history of this disorder or with low screening plasma cortisol levels will be excluded.

In a study of 7-14 days of treatment with mifepristone (10 mg/kg/day) (Laue et al., 1990), no changes

were observed in multiple laboratory measures including complete blood cell count, erythrocyte sedimentation rate, C-reactive protein, antinuclear antibodies (ANA), rheumatoid factor, and multiple quantitative immunoglobulin measures. In multiple subsequent trials of mifepristone, the drug was not associated with significant side effects (Belanoff et al., 2001; Belanoff et al., 2002; Young et al., 2004; Simpson et al., 2005; DeBattista et al., 2006; Flores et al., 2006). In the largest of these trials, psychotically depressed individuals were treated with 600 mg/day of mifepristone (n=105) or placebo (n=116) for one week, followed by usual treatment; there were no significant differences in the incidence of rash or multiple other potential side effects including headache, nausea, vomiting, constipation, dizziness, insomnia, sedation, abdominal pain, or toothache (DeBattista et al., 2006).

Another issue concerns whether it is ethical and safe to enroll veterans in a placebo-controlled medication trial. We believe it is ethically justified in the present trial since FDA-approved pharmacological options for the treatment of PTSD have not been shown to be effective in veterans with PTSD (Hertzberg et al., 2000; Friedman et al., 2007), and since the IOM report concluded that there is no evidence of efficacy for commonly used pharmacotherapies in veterans with PTSD. For safety purposes, many safeguards have been put in place including the exclusion of patients at risk for suicide, frequent monitoring of suicidality and clinical state throughout the project, and the ability of the investigator to adjust medications or treatment plan if needed, without dropping the patient from the study, if his clinical condition deteriorates; these safeguards are described in detail elsewhere (see section 4.i. for details on safety monitoring). Numerous steps have been taken to ensure that patients will be safe and will receive standard pharmacotherapy if necessary. Overall, the proposed study is designed with a favorable risk to benefit ratio for male veterans with PTSD.

As per the medication package insert veterans will be told to swallow the tablets whole. The tablets are quite hard and film coated and therefore difficult to break. Unused tablets will be returned to the Albuquerque CSPCRPCC. Since this drug can cause loss of pregnancy in women, the medication should be kept away from pregnant women and women who could become pregnant.

## 2.b. Significance

It is estimated that 30% of men and 15% of women who served in the Vietnam War developed PTSD (Kulka et al., 1990), and approximately 21% of OIF/OEF veterans seen at the VA from 2002 to 2008 have been diagnosed with PTSD (Seal et al., 2009). Accordingly, there is an urgent need to design treatments that are more effective for this growing population. The significance of this proposal is that it tests a pharmacological approach in PTSD that is innovative in several ways. Whereas most compounds tested for efficacy in PTSD are psychoactive medications developed for other clinical indications and taken daily, this approach seeks to translate clinical research findings into an active treatment by targeting biological alterations consistently linked to PTSD diagnosis and symptom severity. If short-term mifepristone treatment is found to be effective and its effects persist beyond the period of medication intake, it may present a very different approach to pharmacological treatment than chronic psychotropic medication usage. This approach may be preferable to the many veterans with PTSD who do not want to be on psychopharmacological treatments continuously or long-term. Additionally if mifepristone can reverse the HPA axis dysregulation associated with PTSD and its associated behavioral, cognitive and immune alterations, strategies could be developed to favorably alter the long term course of this illness.

## 2.c. Relevance to the VA mission

PTSD is a highly prevalent disorder within the VA population. It is imperative that more effective treatments that lead to recovery from PTSD and its associated cognitive, social, and occupational impairments

are developed. Given the high burden of illness associated with PTSD there is a compelling need to develop novel treatment approaches to reduce the enormous personal and societal costs of this disorder.

## 3. Work Accomplished

The central hypothesis of this application is that increased glucocorticoid receptor sensitivity is an important aspect of HPA axis dysregulation in PTSD. In

Fig. 2 Effect of mifepristone on GR sensitivity in subjects with and without PTSD

[figure not shown]

anticipating this trial, we first obtained information about the effects of mifepristone on peripheral GR sensitivity from participants with (n=8) and without (n=9) PTSD. Mononuclear cells were isolated from blood and divided into two portions. In one portion, cells were incubated with a series of concentrations of DEX. The other portion was incubated with the same concentrations of DEX and 10 $\mu$ M of RU486 (mifepristone). At baseline, the concentration of DEX at which lysozyme activity was inhibited by 50% (i.e., the lysozyme IC50-DEX) was significantly lower in trauma exposed participants with PTSD compared to those without PTSD, indicative of increased peripheral GR sensitivity (4.5  $\pm$  1.5 nM vs. 6.1  $\pm$  0.9 nM; F1,15=6.9, p=0.019). Co-incubation of cells with mifepristone and DEX robustly antagonized the glucocorticoid response as shown in Figure 2. Mifepristone significantly shifted the IC50 in response to DEX antagonized glucocorticoid responsiveness on a measure that is altered at baseline in PTSD, providing evidence that this medication targets a peripheral biological characteristic associated with PTSD.

In order to gain familiarity with mifepristone, we obtained pilot funding from the VISN 3 MIRECC to study a small number of veterans with PTSD using similar inclusion/exclusion criteria to those that are outlined in this protocol. Eight combat veterans with military-related PTSD were treated in a randomized, double-blind trial of mifepristone (600 mg/day) or placebo for seven days and followed longitudinally for one month. The data for each clinical and neuroendocrine outcome measure are shown in Table 1. Based on the clinical response definition of a 12-point or greater decrease in total CAPS score from initial evaluation, all four veterans in the mifepristone group and one of four veterans in the placebo group achieved clinical response at one month follow-up. Similar improvements were observed using the clinical response definition of a 30% decrease in total CAPS-2 score. Three of four veterans in the mifepristone group achieved clinical response at treatment endpoint based on this definition, compared to one of four in the placebo group; these benefits were observed at one month follow-up, as two of four veterans in the mifepristone group maintained clinical response. Furthermore, between groups analysis revealed that the mifepristone group had significantly greater improvements in total CAPS score, CAPS avoidance symptom score, and PCL score at one month follow-up when compared to the placebo group. With respect to neuroendocrine outcomes, mifepristone induced significant acute changes in plasma cortisol (p=0.007), ACTH (p=0.009), and GR binding (p=0.041) from baseline to treatment endpoint; these findings are consistent with successful glucocorticoid receptor blockade. The acute decrease in GR number also points to the possibility increased cortisol binding and signaling. Moreover, this pilot clinical trial had a high retention rate and no adverse events or complaints about study procedures were reported, suggesting that mifepristone treatment is safe, tolerable, and acceptable to veterans with PTSD. Thus, these striking pilot data suggest that treatment with mifepristone is a feasible strategy that may be effective in improving clinical outcomes in veterans with PTSD.

**Table 1: Clinical and Neuroendocrine Outcomes**

|                        |            | Pre-Treatment | Post-Treatment |               | Between Groups Significance |                          |
|------------------------|------------|---------------|----------------|---------------|-----------------------------|--------------------------|
|                        |            | Initial       | Endpoint       | 4-week        | Initial to Endpoint         | Initial to 4-week        |
|                        |            | Mean (SD)     | Mean (SD)      | Mean (SD)     | p-value                     | p-value                  |
| CAPS score             | Drug (n=4) | 68.75 (10.24) | 43.50 (19.49)  | 44.00 (24.12) | 0.425                       | 0.047a |
|                        | PBO (n=4)  | 68.25 (8.77)  | 56.50 (31.89)  | 65.25 (18.86) |                             |                          |
| Intrusive Sx           | Drug (n=4) | 13.75 (8.06)  | 8.00 (7.70)    | 7.50 (9.00)   | 0.463                       | 0.126                    |
|                        | PBO (n=4)  | 14.50 (4.65)  | 12.00 (10.30)  | 15.00 (9.42)  |                             |                          |
| Avoidance Sx           | Drug (n=4) | 29.25 (7.14)  | 18.75 (11.44)  | 17.00 (10.74) | 0.239                       | 0.027b |
|                        | PBO (n=4)  | 28.50 (1.29)  | 25.50 (7.05)   | 26.00 (5.72)  |                             |                          |
| Hyperarousal Sx        | Drug (n=4) | 25.75 (0.50)  | 16.75 (5.56)   | 19.50 (9.68)  | 0.786                       | 0.359                    |
|                        | PBO (n=4)  | 25.25 (6.40)  | 18.25 (10.53)  | 24.25 (5.97)  |                             |                          |
| BDI                    | Drug (n=4) | 22.25 (5.85)  | 13.25 (4.72)   | 11.50 (9.15)  | 0.124                       | 0.769                    |
|                        | PBO (n=4)  | 24.25 (12.12) | 24.75 (10.05)  | 23.75 (9.54)  |                             |                          |
| PCL                    | Drug (n=4) | 60 (10.83)    | 46.75 (11.79)  | 49.25 (15.59) | 0.691                       | 0.200                    |
|                        | PBO (n=4)  | 63.25 (11.41) | 54.25 (24.17)  | 56.25 (16.68) |                             |                          |
| Cortisol ( $\mu$ g/dL) | Drug (n=4) | 13.15 (3.52)  | 31.28 (5.49)   | 11.53 (4.27)  | 0.001c    | 0.786                    |
|                        | PBO (n=4)  | 12.43 (6.16)  | 12.90 (4.87)   | 11.83 (2.91)  |                             |                          |

|                                |            |                  |                  |                  |                          |       |
|--------------------------------|------------|------------------|------------------|------------------|--------------------------|-------|
| ACTH (pg/ml)                   | Drug (n=4) | 49.33 (29.69)    | 153.45 (40.25)   | 53.63 (8.08)     | 0.009d | 0.785 |
|                                | PBO (n=4)  | 30.88 (14.83)    | 38.40 (16.18)    | 41.63 (19.33)    |                          |       |
| Lysosyme IC 50 (nM) | Drug (n=2) | 8.00 (2.55)      | 5.57 (.76)       | 6.73 (3.66)      | 0.162                    | 0.411 |
|                                | PBO (n=4)  | 3.27 (2.89)      | 3.65 (2.06)      | 5.03 (1.68)      |                          |       |
| GR/cell                        | Drug (n=3) | 1557.67 (539.75) | 188.67 (116.89)  | 1593.00 (770.02) | 0.003             | 0.322 |
|                                | PBO (n=4)  | 1019.50 (553.91) | 1243.00 (543.84) | 1824.75 (683.80) |                          |       |

aMedian change in score for mifepristone group (20.0); median change in PBO group (10.5); non-parametric p-value (0.021)

b Median change in score for mifepristone group (11.0); median change in PBO group (4.0); non-parametric p-value (0.028)

c Median change in cortisol for mifepristone group (17.2); median change for PBO group (0.4); non-parametric p-value (0.021)

d Median change in ACTH for mifepristone group (90.6); median change for PBO group (4.2); non-parametric p-value (0.021)

## 4. Work Proposed

### 4.a. Overview

90 eligible male veterans with chronic PTSD will be randomly assigned to treatment with 600 mg/day mifepristone or placebo for one week and assessed for clinical outcomes at one and three months follow-up. Eligibility will be based on the inclusion and exclusion criteria which are enumerated below and in the Human Participants section. The inclusion and exclusion criteria were selected in order to include as representative a sample as possible while also addressing safety concerns. Veterans who are actively suicidal as assessed by the Columbia-Suicide Severity Rating Scale (C-SSRS) or who have attempted suicide within the past two years will be excluded. (If suicidality is identified, the necessary steps will be taken to ensure the appropriate clinical care is provided, and the local suicide prevention policies implemented.) Veterans with adrenal insufficiency will be excluded, as will veterans with other major medical or neurological illnesses, as they may be at increased risk of developing adverse events. Veterans with renal disease/impairment, hepatic disease/impairment, cardiac illness (e.g. coronary vascular disease, congestive heart failure), or hypokalemia at screening will also be excluded. Since mifepristone use can prolong the QTc interval in a dose-related manner, veterans with a prolonged QTc interval, defined as >450 msec, on the ECG at screening will be excluded. To evaluate QTc prolongation post-mifepristone treatment, an ECG will also be performed at both the 3 day follow up visit (visit 1.5) and 1 week follow-up visit (week 1, visit 2).

Participants on potent CYP3A4 inhibitors (fluconazole, ketoconazole, itraconazole, erythromycin, rifampin) and some anticonvulsants (e.g., phenytoin, phenobarbital, and carbamazepine) will be excluded since these medications impact the metabolism of mifepristone (see Risk/Benefit Assessment for details). Due to an increased risk of adverse drug reactions, veterans taking simvastatin, lovastatin, fentanyl, pimozone, bupropion, nefazodone, dihydroergotamine, ergotamine, quinidine, sirolimus, carvedilol, propranolol, diltiazem, verapamil, alprazolam, or tacrolimus will also be excluded. Since the impact of mifepristone on the male reproductive system has not been extensively studied, only veterans willing to use effective means of birth control for up to 90 days after mifepristone ingestion will be eligible; this will cover the critical period of fetal development.

For veterans prescribed psychotropic medications (i.e., antidepressants, antipsychotics or anxiolytics/sedative-hypnotics), the veteran is required to be on a stable dose for at least five weeks prior to screening. For veterans not taking psychotropic medication, a minimum of five half-lives must elapse prior to screening since the veteran last took any given psychotropic medication. Should it be necessary to adjust a patient's treatment regimen during the 3 month treatment period, standard pharmacological care for PTSD will be instituted. Major depression and other anxiety disorders are not exclusionary since they frequently co-occur with PTSD and it remains unclear whether their presence represents true comorbidity, symptom overlap, or severe illness. Since mild head trauma is common in the military population in general, excluding such participants would diminish the generalizability of the sample; participants with severe traumatic brain injury (TBI), defined as an extended period of unconsciousness or amnesia following injury, will be excluded. The Ohio State University (OSU) TBI Identification Method will be used to assess lifetime history of TBI. This method first establishes all significant injuries in one's life and then determines if a TBI may have occurred based on whether the participant experienced a loss of consciousness (LOC) and, if so, for how long. A person is said to have a mild TBI if LOC does not exceed 30 minutes for any injury, a moderate TBI if LOC is between

30 minutes and 24 hours, and a severe TBI if LOC exceeds 24 hours. The OSU TBI assessment will be administered by a trained rater during the psychiatric evaluation conducted at screening.

Additionally, veterans diagnosed with alcohol/substance abuse and dependence will be excluded only if they are recently engaged in a maladaptive pattern of use or abuse. More specifically, persons who meet diagnostic criteria for alcohol/substance dependence will be excluded if they have manifested dependence within the previous three months (i.e., have met three or more of the seven criteria for a maladaptive pattern of use in the last three months). Persons with alcohol/substance abuse (who, by definition, do not meet criteria for alcohol dependence) will be excluded if they have shown a maladaptive pattern of alcohol use during the past one month (i.e., have met one or more of the four criteria for a maladaptive pattern of abuse).

Veterans who are currently receiving psychotherapies - individually or in a group setting - that are considered to have significant benefit for PTSD, according to the VA and DoD's Treatment Guidelines, will also be excluded. These therapies are cognitive therapy for PTSD (e.g. cognitive processing therapy (CPT)), exposure therapy (e.g., prolonged exposure therapy), stress inoculation training, and eye movement desensitization and reprocessing (EMDR). Other forms of therapy and case management which do not specifically target PTSD symptoms and/or have not been shown to provide significant benefit in PTSD will be allowed at entry and throughout the study (e.g. supportive therapy, psychodynamic therapy, anger management, cognitive behavioral therapy for symptoms or problems other than PTSD).

We recognize that PTSD in women is increasingly common and effective treatments are needed for this group as well. However, women will be excluded from this initial trial for safety reasons, since mifepristone is an abortifacient. Should mifepristone prove to be effective in male veterans with PTSD, this would provide a rationale for future studies in women, employing additional safeguards.

#### 4.a.1. Inclusion Criteria

1. Participant is a male veteran.
2. Veteran meets DSM-IV diagnostic criteria for chronic PTSD.
3. Veteran has a CAPS total score (past month symptom status) greater than or equal to 50 at screening.
4. For veterans taking psychotropic medications (i.e., antidepressants, antipsychotics or anxiolytics/sedative-hypnotics), the veteran will be on a stable dose for at least five weeks prior to screening.
5. For veterans not taking psychotropic medication, a minimum of five half-lives must elapse prior to screening since the veteran last took any given psychotropic medication.

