In a VA-commissioned review of the state of treatment of PTSD, the Institute of Medicine (IOM) did not find evidence to support the efficacy of commonly used psychotropic medications (IOM, 2008). This is of particular concern since pharmacotherapy is a major treatment modality for PTSD in the VA. Among veterans who initiate PTSD treatment at the VA, 50% are prescribed psychotropic medication within the first year (Spoont et al., 2010); among veterans in chronic care for PTSD, 80% are receiving psychotropic medications (Mohamed and Rosenheck, 2008). The vast majority are prescribed an antidepressant, primarily selective serotonin reuptake inhibitors (SSRIs). However, controlled trials have not found SSRIs to be effective in PTSD (Hertzberg et al., 2000; Friedman et al., 2007). In a 12 week placebo-controlled trial of sertraline in veterans, active treatment was not associated with improvements in PTSD, its associated symptoms (depression, anxiety, sleep disturbance), or quality of life (Friedman et al., 2007). Antipsychotics, mood-stabilizers, sedatives, and hypnotics are also widely used, alone and in combinations, despite limited efficacy data and some concerns regarding safety (e.g., metabolic and neurologic side effects). The extensive use of polypharmacy, incorporating off-label medications and medications that have not been shown to be effective, highlights the limitations in the current psychopharmacological approach to PTSD. There is clearly a need to develop more effective pharmacological treatments. Whereas the medications that are widely used to treat PTSD were developed for use in other disorders and are prescribed for long-term use, medication strategies that specifically target PTSD symptoms and/or pathophysiology may be more effective and possibly even curative. Therefore, we propose to examine whether targeting hypothalamic-pituitary-adrenal (HPA) axis dysregulation in PTSD with mifepristone – which recalibrates the HPA axis through peripheral and central mechanisms – will be of therapeutic benefit.

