The team at Durham has a vast amount of experience with randomized controlled medication studies in PTSD and is well versed in performing the assessments and evaluations that will be used in the present study. For CSP 504, Durham was the second site in terms of recruitment (26 participants in 36 months). Additionally, Durham has participated in eight other trials: 1) CSP 563 recruited 13 participants in 15 months; 2) “A Pilot Randomized Controlled Trial in Sub-threshold PTSD with Paroxetine in Veterans who Served after September 11, 2001” recruited 12 participants in one year; 3) “Bupropion SR for Social and Occupational Dysfunction, Symptom Reduction, and Smoking Cessation in PTSD” recruited 30 participants in two years; 4) “A Placebo-Controlled Evaluation of the Effects of Bupropion for Smoking Cessation in Patients with PTSD” recruited 15 participants in one year; 5) “Lamotrigine in the Treatment of PTSD” recruited 8 participants in one year; 6) “Preliminary Study of Nefazodone in PTSD” recruited 10 participants in one year; 7) “Double-Blind Comparison of Sertraline and Placebo in Outpatients with PTSD” recruited 22 participants in two years; and 8) “Fluoxetine Treatment of PTSD” recruited 11 patients in 18 months.

San Diego is an active research site with a large patient population and high retention and completion rates for participants enrolled in clinical trials. The San Diego site PI, [name], has been an investigator in seminal pharmacotherapy trials in PTSD including: 1) “A Double-Blind, Randomized, Placebo-Controlled, Multi-Center Study of Brofaromine in the Treatment of PTSD;” 2) “Sertraline Treatment of PTSD: A Randomized Controlled Trial;” and 3) “Randomized, Double-Blind Comparison of Sertraline and Placebo for PTSD in a Department of Veterans Affairs Setting.” Additionally, San Diego has participated in three large, multi-site trials: 1) CSP 519 (“Integrating Practice Guidelines for Smoking Cessation Into Mental Health Care for PTSD”) recruited 88 participants in 36 months; 2) CSP 504 recruited 19 participants in 25 months; and 3)

“A Randomized, Placebo-Controlled Trial of Nepicastat for the Treatment of PTSD in OIF/OEF Veterans” recruited 9 participants in 11 months.

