Albuquerque has been one of the top recruitment sites for two CSP studies in PTSD: CSP 563 (“Prazosin and Combat Trauma”, having recruited 12 participants in 11 months) and CSP 504 (“Risperidone Treatment for Military Service Related Chronic PTSD”, 14 participants in 30 months). Recruitment was also high in other PTSD studies. However due to low recruitment in this study, this site was terminated in March, 2015. Salisbury and Little Rock were added in April 2015, instead, to help recruitment.

Salisbury VAMC was a very successful site for CSP 563 (“Prazosin and Combat Trauma”). It is also home to a MIRECC dedicated to the study of post-deployment mental health problems including PTSD and mTBI. It has a full research infrastructure and ready-access to the study group of interest.

Little Rock VA has just successfully recruited for and completed several studies of PTSD focused on a similar participant pool. One was a randomized controlled trial of modafanil in OEF/OIF combat veterans with PTSD (25 subjects completed the RCT over an 18 month recruiting period). [name], the site investigator, was also the collaborating psychiatrist on “Telemedicine-based collaborative care for posttraumatic stress disorder: a randomized clinical trial” and facilitated a study examining psychophysiological measures in OIF/OEF veterans.

We propose to enroll 90 participants across multiple VA sites to yield 72 completers based on an estimated attrition rate of 20%. We expect the 3 active sites (Bronx, San Diego, and Durham) to enroll 25~26 patients each over the course of 31 months (0.8 per site per month); and the 2 added sites (Salisbury and Little Rock) to enroll 5~6 patients each over the course of 9~10 months (0.5~0.6 per site per month). The Albuquerque site that was terminated in February 2015 enrolled a total of 2 participants.

Given the data provided by the VHA Support Services Center and the individual study sites, this recruitment goal, which takes into account the challenges of recruiting unmedicated veterans and stably medicated veterans, is feasible.

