##### Primary Outcome:

Primary Analysis of Primary Outcome -The primary analysis for this study will not be based on a hypothesis test; rather, responder rates at one month will be calculated for each of two groups. If mifepristone 600 mg is observed to have at least a 15% higher responder rate than placebo, then we are at least 90% certain we have detected a clinically relevant signal. This analysis will be performed based on a modified intent-to-treat (mITT) principle. All randomized participants will be included in the analyses except for those for whom there is positive proof that they did not take a single dose of study medication (e.g. medication never picked up, full bottle returned, patient immediately declines participation after study medication has been dispensed) or there is positive proof that they are deemed ineligible after randomization and are terminated in the 7-day treatment phase due to safety concern. For patients who do not have one-month CAPS total score, their responses will be estimated using multiple imputation technique as outlined in Molenberghs and Kenward, 2007, Chapter 9 and implemented in the SAS procedure MI using participants aforementioned baseline characteristics and available information at other time points (baseline, 1 week, 12 week). The imputation will be done within each treatment group.

Secondary Analysis of Primary Outcome -The primary outcome will also be compared using chi-square tests. Additionally, logistic regression models will be used to adjust for aforementioned baseline characteristics. The model selection will use a backward elimination procedure and be verified by a forward selection procedure.

Exploratory Analysis of Primary Outcome -The primary outcome will also be explored for subgroups as defined by concurrent psychotropic medication use status and classification prior to randomization. The mITT principle will also be applied in the secondary and exploratory analyses of the primary outcome.

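### The closed list that defines psychotropic medication leaves out mood stabilizers, so a recently started or changed one escapes the entry rules on stable dose and washout

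*Protocol*

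**What the plan says.** **Entry rules.** Inclusion criterion 4 (section 4.a.1) reads, for veterans taking "psychotropic medications (i.e., antidepressants, antipsychotics or anxiolytics/sedative-hypnotics), the veteran will be on a stable dose for at least five weeks" before screening. Section 4.a says the same: "For veterans prescribed psychotropic medications (i.e., antidepressants, antipsychotics or anxiolytics/sedative-hypnotics), the veteran is required to be on a stable dose". Both introduce the three classes with i.e., which makes the list a definition. Elsewhere, as with the anticonvulsants and the psychotherapies in 4.a, the protocol writes e.g. when it means examples. Inclusion criterion 5 rests on the same term: for men not taking such a drug, "a minimum of five half-lives must elapse prior to screening since the veteran last took any given psychotropic medication".

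**Background.** Section 1.a, in its paragraph on psychotropic medication for PTSD, names antidepressants and then says: "Antipsychotics, mood-stabilizers, sedatives, and hypnotics are also widely used".

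**Exclusions.** Exclusion 3 removes three anticonvulsants: phenytoin, phenobarbital and carbamazepine. The Risk/Benefit Assessment explains this by their effect on mifepristone metabolism, not by symptom stability.

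**Analysis.** Section 4.p.1 uses concurrent psychotropic medication as a baseline characteristic (yes/no and number of drugs), and through that list as a predictor in the multiple imputation and a candidate in the logistic model. It is also a covariate in the mixed model and the basis of the exploratory "subgroups as defined by concurrent psychotropic medication use status and classification prior to randomization". A between-arm comparison of medication change uses the term again. None of these places repeats or widens the three-class list.

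**The concern.** The stability and washout rules are there so that a change in CAPS between baseline and week 4 is not caused by some other recent drug change. Section 4.g shows the same intention after entry: it discourages treatment adjustments, above all in the first month, because they could confound the primary endpoint. A definition that leaves out a class which the protocol itself calls widely used opens that route at entry.

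Two things are at stake. The first is eligibility: men may be enrolled while their symptoms are still moving in response to another drug, and nothing done at analysis can undo that. The second is conditional. If the narrow list also serves as the coding rule in 4.p, the medication variables will be wrong for some men.

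**Working it through.** This is mainly a check of text against text.

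**1. Classes named in 1.a against classes in the list**

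| Class in 1.a | In the 4.a and inclusion 4 list? |
|---|---|
| Antidepressants | Yes |
| Antipsychotics | Yes |
| Sedatives, hypnotics | Yes (anxiolytics/sedative-hypnotics) |
| Mood stabilizers | No |

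**2. Is the gap closed elsewhere?** Exclusion 3 catches carbamazepine, phenytoin and phenobarbital. Lithium, valproate and lamotrigine appear on no exclusion list.

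**3. A literal case.** A man takes lamotrigine, started or changed the week before screening. It belongs to none of the three classes, so inclusion 4 does not ask for stability and inclusion 5 does not ask for washout. A man who stopped the drug in that week passes as well.

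**4. Consequences in 4.p, if the list is carried over**

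- Only drug is a mood stabilizer: coded as not on psychotropics.
- Antidepressant plus mood stabilizer: still coded as medicated, with a drug count one too low.
- Mood stabilizer added to a stable antidepressant after entry: not a new psychotropic, so possibly not a change.
- Man unmedicated at entry who seeks a rescue medication: counted, because that limb of the definition has no class restriction.

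**5. Size.** The plan's own figure comes first. With 36 completers per arm and response rates of 40% and 55%, the probability of correct selection is

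Φ(0.15 / √[(0.40×0.60 + 0.55×0.45)/36]) = Φ(0.15/0.1164) = Φ(1.289) = 0.901,

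which agrees with the stated 90%. The finding does not depend on it.

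The protocol gives no share of men on unlisted drugs. As an assumption only, take 5–20% of 90:

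- 0.05×90 = 4.5 to 0.20×90 = 18 men on an unlisted drug. This is an upper bound on misclassification in the yes/no variable, because a man who also takes a listed drug stays correctly coded.
- If one in five of them is not stable (also assumed): 0.9 to 3.6 men, or 1% to 4% of 90.
- As a deliberately harsh case, suppose these men respond at 40% in both arms. The expected difference falls from 15 points to 15×0.99 = 14.85 or 15×0.96 = 14.4 points.
- At 14.4 points: Φ(0.144 / √[(0.24 + 0.544×0.456)/36]) = Φ(0.144/0.1164) = Φ(1.237) = 0.892. At 14.85 points the result is 0.899.

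Under these assumptions the selection probability falls from 0.901 to between 0.899 and 0.892.

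**The case against.** The strongest case against the point is that it is a small drafting gap with existing safeguards. Section 4.i records every concomitant drug with daily dose, indication and dates, so drugs can be re-coded for analysis. Exclusion 6 removes lifetime type I bipolar disorder, schizophrenia and schizoaffective disorder, which should lower the number of men on mood stabilizers. Exclusion 11 lets the site investigator refuse anyone judged unsuitable. The subgroup is exploratory, and the protocol calls the results hypothesis generating.

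Most of this stands and limits the size of the point. It does not close the gap. Re-coding cannot reverse enrolment on an unstable regimen, and discretion at each site is not a uniform entry rule. A statistical analysis plan, which is not shown here, could define the analysis variable but could not change eligibility.

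A reader might infer more than the protocol supports:

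- *That men on unlisted drugs are analysed as unmedicated.* Section 4.p does not repeat the list, and 1.a discusses mood stabilizers as psychotropics, so a wider reading there is open. Even on the narrow reading, only men with no listed drug are affected.
- *That new prescriptions go uncounted.* The rescue limb of the change definition is not tied to the three classes.
- *That the primary result is biased.* Allocation is randomized and double-blind, so instability before entry is expected in both arms. The primary rule compares responder rates, and medication status enters it only as one imputation predictor among many.
- *That omitting prazosin contradicts the protocol.* Prazosin and lamotrigine appear only in titles of earlier PTSD trials in the site histories of the recruitment and feasibility section ("Prazosin and Combat Trauma", "Lamotrigine in the Treatment of PTSD"). The protocol never calls prazosin psychotropic. These titles make use in this population plausible, and no more than that.

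**Conclusion.** The point holds for mood stabilizers. The protocol fixes the definition of psychotropic medication in two places, fixes it more narrowly than its own background section, and so leaves a recently changed mood stabilizer outside both entry rules. Because the rule is stated, this is not a detail left for later.

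The consequence for the primary comparison is added noise of unknown, probably small, amount, with no expected direction. The consequence for the covariate, drug count, subgroup and medication-change comparison is conditional on the same list being used in 4.p. The ranges shown rest on assumed prevalence and instability and are not estimates from the documents. The case for acting is that the repair is cheap and that the eligibility part cannot be repaired after enrolment.

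**What to change.** 1. Reconcile the list in section 4.a and inclusion criterion 4 with the classes named in section 1.a, so that mood stabilizers are covered by the term on which inclusion criteria 4 and 5 depend.
2. State explicitly whether other drugs prescribed for PTSD symptoms, such as prazosin, fall under the term.
3. Refer to that single definition in 4.p.1 wherever the term is used: the baseline characteristic and drug count, the imputation predictor, the logistic and mixed-model covariate, the exploratory subgroup and the medication-change comparison.

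The cost is the wording of one criterion, its counterpart in 4.a and one analysis definition. Some men will be deferred or fail screening who would otherwise have entered. No new data are needed, since all concomitant drugs are already recorded.
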